## 1 ABBREVIATIONS

|       |                                    |
|-------|------------------------------------|
| DMFS  | Distant Metastatic Free Survival   |
| RFS   | Relapse Free Survival              |
| OS    | Overall Survival                   |
| CMM   | Cutaneous Malignant Melanoma       |
| GCP   | Good Clinical Practice             |
| eCRF  | electronic Case Report Form        |
| CTIS  | Clinical Trials Information System |
| EDC   | Electronic Data Capture            |
| HR    | Hazard Ratio                       |
| PI    | Principal Investigator             |
| WOCBP | Women of child-bearing potential   |

## 2 SYNOPSIS

|                                                                                                                                                                                                                         |                                                                                                                                                                                                                                                               |
|-------------------------------------------------------------------------------------------------------------------------------------------------------------------------------------------------------------------------|---------------------------------------------------------------------------------------------------------------------------------------------------------------------------------------------------------------------------------------------------------------|
| Clinical Trial Title: A prospective randomized international multicenter study to compare Short versus Long Adjuvant immunotherapy after radical surgery of stage IIb-c, III and IV cutaneous malignant Melanoma |                                                                                                                                                                                                                                                               |
| Short Title:
Assessment of short immunotherapy after radical surgery of high-risk malignant melanoma.                                                                                                         |                                                                                                                                                                                                                                                               |
| EU CT number 2023-509994-22-00                                                                                                                                                                                   |                                                                                                                                                                                                                                                               |
| Clinical Trial phase                                                                                                                                                                                             | III                                                                                                                                                                                                                                                           |
| Clinical Trial Population                                                                                                                                                                                        | Patients radically operated for stage IIb-c, III and IV cutaneous malignant melanoma (CMM)                                                                                                                                                                    |
| Clinical Trial objective                                                                                                                                                                                         | To assess whether treatment (adjuvant +/- neoadjuvant) with immunotherapy for 6 months is as effective as 12 months.                                                                                                                                          |
| Clinical Trial design                                                                                                                                                                                            | Randomized non-inferiority                                                                                                                                                                                                                                    |
| Study population/indication and total number of subjects (Planned)                                                                                                                                               | As a screen failure rate of approximately 10 percent is anticipated, screening of approximately 2000 subjects is planned to achieve the target of 1880 subjects in total (940 subjects randomized to treatment in each arm).                                  |
| Number of planned clinical trial centers                                                                                                                                                                         | Around <del>630</del>                                                                                                                                                                                                                                         |
| Clinical trial duration                                                                                                                                                                                          | The planned clinical trial duration (from First Subject First Visit to Last Subject Last Visit) is approximately nine years.
The planned duration of recruitment (from First Subject First Visit to Last Subject First Visit) is approximately four years. |
| Definition of End of Trial                                                                                                                                                                                       | The trial ends when the last subject has completed the last follow-up (planned Dec 2033).                                                                                                                                                                     |
| Duration of subject participation                                                                                                                                                                                | Each subject will be followed for overall survival for at least five years.                                                                                                                                                                                   |
| Key Inclusion criteria                                                                                                                                                                                           | 1) Performance status ECOG/WHO 0-1.
2) Radical surgery for CMM stage IIb-c, III and IV.                                                                                                                                                                    |
| Key Exclusion criteria                                                                                                                                                                                           | 1) The patient is assessed as unfit to receive immunotherapy.
2) An active, known, or suspected autoimmune disease.                                                                                                                                        |
| Investigational product                                                                                                                                                                                          | Standard immunotherapy (adjuvant +/- prestudy neoadjuvant), currently nivolumab or pembrolizumab administered intravenously subcutaneously for 12 months.                                                                     |
| Comparator                                                                                                                                                                                                       | Standard immunotherapy (adjuvant +/- prestudy neoadjuvant), currently nivolumab or pembrolizumab administered intravenously or subcutaneously for 6 months.                                                                   |
| Endpoints                                                                                                                                                                                                        | Primary efficacy endpoints are distant metastatic free survival (DMFS) and relapse free survival (RFS) at 2 years.
Secondary efficacy endpoints are long-term DMFS, RFS and overall survival.                                                              |
| Principal statistical method                                                                                                                                                                                     | Cox regression model                                                                                                                                                                                                                                          |
| Sample size calculation                                                                                                                                                                                          | 1880 patients                                                                                                                                                                                                                                                 |

### 3 BACKGROUND AND RATIONALE

The incidence of cutaneous malignant melanoma (CMM) is rapidly increasing in Western Europe, not the least in Sweden. Between 2013 and 2023 the increase was over 60 %, from 3400 to 5500 cases per year in Sweden. According to the Swedish Cancer Society, the number of cases is expected to multiply during the next decades ([www.cancerfonden.se](http://www.cancerfonden.se)). As there are no clear trends of earlier detection of CMM, the number of patients that will be eligible for systemic adjuvant treatment will probably continue to steadily increase.

Since 2017, post-operative treatment with PD-1 inhibitors for 12 months is routine in the Western world for stage III melanoma patients. However, a rationale for having chosen a 12-month treatment period in the registration studies is lacking. The introduction of adjuvant immunotherapy for high-risk patients was based on two pivotal phase III randomized studies, CheckMate 238 (nivolumab, Opdivo®) and the other, Keynote 054, (pembrolizumab, Keytruda®) where the former also included stage IV patients (1, 2). In 2023, results from two large, randomized phase III studies assessing immunotherapy in patients operated for thick CMM without lymph node involvement (stage IIb-c) (Keynote 716 and Checkmate 76K) were presented. The results showed that treatment with PD-1 inhibitor significantly prolonged relapse free survival (RFS) compared to placebo (3, 4). Results from neo-adjuvant studies with PD-1 + CTLA-4 inhibitor (OpACIN) have shown promising results but they are small and lack a control arm (5). In addition, results from a randomized phase II study in patients with macroscopic stage III and operable stage IV CMM were published earlier last year showing that the event-free survival was significantly better for patients receiving treatment with neoadjuvant PD-1 inhibitor compared to the standard adjuvant treatment. Patients in the experimental arm received two months of preoperative and ten months of post-operative immunotherapy (6). The ~~ongoing~~ phase III NADINA study ~~aims to confirm~~ the increased benefit of neoadjuvant compared to adjuvant immunotherapy. In this trial, adjuvant treatment ~~was~~ not given to patients where a complete or near complete pathological response on neoadjuvant treatment has been achieved ([ClinicalTrials.gov: NCT04949113](https://clinicaltrials.gov/ct2/show/study/NCT04949113)). Other differences compared to the phase II study is that the patients in NADINA received combination immunotherapy neoadjuvant and that patients with a BRAF-mutated tumor received BRAF and MEK inhibitors adjuvant (7).

Noteworthy, no randomized study has investigated whether a shorter adjuvant treatment is as effective as 12 months. In addition, according to “Clinicaltrials.gov”, there is no study addressing this issue.

There are ongoing studies assessing new drugs in the adjuvant setting for high-risk malignant melanoma patients. ~~Two phase III studies investigate the potential benefit of adding the LAG-3 inhibitor finalimab to anti PD-1 treatment (cemiplimab, Libtayo®) : In RELATIVITY-098, relatlimab is given together with nivolumab (Opdualag®) (NCT05002569) while finalimab is tested together with cemiplimab (R3767-ONC-2011, Libtayo®) in a phase III the other study (NCT05608291). Furthermore, whether pembrolizumab in combination with the TIGIT inhibitor, vibostolimab is more effective than pembrolizumab alone is addressed in another large study (KEYVIBE010, NCT05665595).~~ There is yet another potential registration study (INTERpath V940-001, NCT05933577) where patients who have undergone surgery for different stages of high risk CMM, receive pembrolizumab combined with multiple injections with a neoantigen mRNA-based vaccine. Promising results with this personalized vaccine candidate was shown in a randomized (2:1) phase 2 study, KEYNOTE-942 (NCT03897881) (5). ~~All these trials use a 12-month treatment period despite the lack of evidence.~~

The BRAF and MEK inhibitors dabrafenib and trametinib are alternative adjuvant treatments for patients with BRAF mutated CMM (8). Therapy with the BRAF and MEK inhibitors, encorafenib + binimetinib is being evaluated in another randomized phase III study, COLUMBUS-AD (NCT05270044), in patients who have had radical surgery for thick CMMs without lymph node involvement.

In recent years, adjuvant systemic immunotherapy has been introduced for several other cancer types including non-small cell lung cancer (NSCLC), bladder cancer, renal cancer and esophageal cancer. Interestingly, studies of adjuvant treatment shorter than 12 months have not been conducted in these patient groups either. One plausible reason is that adjuvant studies usually have been conducted with pharmaceutical companies as sponsors.

The adjuvant systemic treatment in colorectal cancer patients is not immunotherapy but 5-FU based chemotherapy. It is noteworthy that in these patients, the length of the adjuvant treatment period has

been reduced gradually from two years to one year to 6 months and presently to 3 months if an oxaliplatin-containing regimen is used based on results from large non-inferiority trials (9).

## 4 TIME SCHEDULE

2023-2024: Planning, fund-raising, writing the final protocol, setting up the electronic case report form (eCRF) and randomization procedure, gaining ethical committee, radiation protection committee and the Swedish Medical Products Agency approvals.

2023-2024: Recruitment of centers.

2024-2028: Enrollment of patients.

2033: Last patient followed-up for 5 years.

## 5 AIM AND HYPOTHESIS

The aim is to conduct a prospective non-inferiority randomized international multicenter study with systemic immunotherapy comparing treatment with a duration of 6 months (experimental arm) to 12 months (standard arm) in patients having undergone radical surgery for stage IIb-c, III and IV CMM. The primary aim is to address whether 6 months of immunotherapy (adjuvant +/- neoadjuvant) in these high-risk patients is as effective as the current 12-month scheme. The primary outcome variables are distant metastatic free survival (DMFS) and RFS at 2 years.

The hypothesis is that 6 months of systemic immunotherapy (adjuvant +/- neoadjuvant) is as effective as the current standard treatment scheme of 12 months in patients who undergo radical surgery for high risk CMM.

## 6 EVALUATION OF RISK AND BENEFIT

With the adjuvant standard treatment today for patients with high-risk CMM, the number needed to treat (NNT) to prevent relapse is roughly seven while adverse reactions grade III-IV develop in around 1/7 patients. This means that the likelihood of benefit equals the risk for developing severe side effects.

If the results show that a shorter treatment period is as effective as the current one-year scheme it would greatly benefit the patients by decreasing the risk for side effects and by reducing the number of hospital visits. In addition, the health care resources saved would enable spending more resources in other areas. The Swedish Melanoma Patient Group (Melanomföreningen) has been addressed and they are in favor of the study, although they anticipate that patients might not want to participate due to fear of receiving an inferior treatment. However, none of the registration studies have so far shown that adjuvant systemic therapy in CMM patients significantly prolongs overall survival (OS)

and its routine use is based on prolonged RFS. As in other malignancies, adjuvant treatment for CMM is most often given in vain as many patients would not relapse even without adjuvant treatment and a large group of patients relapses despite having received adjuvant treatment. Complete response is achieved in around 20 % of metastatic CMM patients and these responses are usually long lasting. This raises the question whether it might be better to refrain from adjuvant immunotherapy and instead save this treatment for those patients who relapse with advanced disease. The patients in whom we prevent relapse by adjuvant immunotherapy may be the same patients who gain from immunotherapy with complete response in the advanced setting. In addition, a recent cohort study did not indicate any OS benefit after the introduction of immunotherapy (11). Importantly, an interim analysis will be conducted to ensure that the experimental arm (6 months of treatment) is not clearly inferior to the standard treatment period of 12 months, in which case the trial recruitment will be halted. Noteworthy, similar studies have been conducted in breast and colorectal cancer patients where adjuvant treatment significantly prolongs OS.

## 7 RECRUITMENT AND ELIGIBILITY

### 7.1 RECRUITMENT

Patients will be recruited from treating centers in Sweden and ~~university~~ clinics in other countries, preferably university centers in ~~European countries~~. At each participating center, consecutive patients receiving radical surgery for high-risk CMM will be considered for inclusion.

Based on data from the Swedish Melanoma Registry (SweMR), the expected incidence of stage IIIb-d according to AJCC8 classification at the time of diagnosis, is 250 patients/year.

With a recruitment rate of 60%, 150 patients are estimated to be enrolled/year in Sweden only.

In addition, CMM patients diagnosed with stage III at relapse are also candidates for systemic adjuvant treatment. Unfortunately, the annual incidence of patients diagnosed as stage III at relapse is currently not recorded in Sweden. The small number of patients undergoing radical surgery for stage IV CMM is also unknown.

No Swedish stage IIb patients are anticipated to participate since they are not covered by the national recommendation.

We estimate that 50 patients from these subgroups will be included yearly, yielding a total recruitment of 200 patients/year.

## 7.2 INCLUSION CRITERIA

- 1) Provision of written informed consent for participation.
- 2)  $\geq 18$  years of age.
- 3) Performance status ECOG/WHO 0-1.
- 4) Adequate organ functions as per standards for immunotherapy.
- 5) Radical surgery for CMM (including acral) stage IIb-c, III (including in transit) and IV. Stage III CMM patients with unknown primary and stage IIb-c CMM patients who have not undergone sentinel node procedure are eligible.
- 6) A complete physical examination within 28 days prior to start of study treatment randomization.
- 7) Previous adjuvant treatment with BRAF + MEK inhibitors is allowed.
- 8) Neoadjuvant treatment with immunotherapy for two months (currently pembrolizumab every third weeks three times or nivolumab every fourth week two times) is allowed providing that a complete or near complete pathological response was not achieved ~~and patients with clear progressive disease according to the pathology report are not eligible~~.
- 9) All participants who have not received neo-adjuvant treatment must have disease-free status documented by radiological assessment within 28 days prior to start of study treatment randomization while ~~8~~ 6 weeks is sufficient for neo-adjuvant treated patients.
- 10) The patient must be randomized and start systemic study treatment within 12 weeks after final surgery (including neoadjuvant patients), i.e. excision + sentinel node biopsy, lymph-node dissection or metastasectomy.
- 11) ~~10~~ Participants must be off immunosuppressive doses of systemic steroids ( $>10$  mg/day prednisone or equivalent) for a minimum of 14 days prior to start of study treatment drug administration.
- 12) ~~11~~ Sufficient renal function for radiological assessments with i.v. contrast.
- 13) ~~12~~ Peri-operative radiation therapy is allowed.
- 14) ~~13~~ Patients who experience a locoregional lymph node relapse, i.e. stage III disease or operable stage IV at a time-point later than primary diagnosis are welcome to participate provided that they have not received neoadjuvant and/or adjuvant immunotherapy.
- 15) ~~14~~ Negative highly sensitive urine or serum pregnancy test for women of childbearing potential (WOCBP)
- 16) ~~15~~ WOCBP are required to use contraceptives as described below (section 7.2.1)

176) Male subjects should agree to use condom during treatment and for three (3) months after termination of treatment

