## 8 STUDY PROCEDURES

### 8.1 RANDOMIZATION PROCEDURE

Randomization 1:1 will be locally performed in the electronic data capture (EDC) system (Viedoc) before start of adjuvant treatment and stratified according to tumour stage, and neoadjuvant treatment given or not, type of neoadjuvant treatment (PD-1 inhibitor or ipilimumab + nivolumab) treatment and pathological response (partial or non-response) after neoadjuvant treatment.

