## **1.4 STUDY FOLLOW-UP SCHEME**

The schedule of assessments is listed in Appendix 1.

A baseline visit 1-11 weeks after the last melanoma-related surgery is scheduled for study information, inclusion and randomization. The national routine schedule for follow-up visits will be

applied for all patients in the study according to standard practice which normally includes doctor appointments with physical examinations after each radiological assessment.

The scheme includes compulsory imaging [including brain](#) at baseline (within 4 weeks [for adjuvant and 8 weeks for neoadjuvant respectively](#) of [study treatment start](#)~~randomization and including brain~~), and at 6 and 24 months (~~including brain~~) respectively (see flow-chart below). The minimum imaging scheme is similar to Swedish guidelines but clearly less extensive than current practice in most other countries, e.g. Great Britain ([name], personal communication) and much more frequent imaging was done in previous adjuvant studies (1, 2). Swedish patients will undergo one extra scan (at 24 months) compared to national guidelines which corresponds to (Uppsala University Hospital as reference) an additional radiation dose of 12 mSievert (dose for CT scan) or 6 mSievert (dose for FDG-PET-CT). The mode of imaging (CT scan of the thorax, abdomen and brain/MRI brain or i.v. contrast enhanced whole body FDG-PET-CT including brain or whole body FDG-PET-CT and MRI brain) is chosen by the investigator at baseline and preferably, the same method is used for all imaging. Importantly, if an FDG-PET-CT without contrast or CT not including brain is conducted at 24 months, MRI of the brain must also be performed. If the primary CMM was situated on one leg, the FDG-PET-CT must include the site of the primary tumour. In case of a positive sentinel node but no performed lymph node dissection, CT imaging must include local lymph nodes.

All patients will be followed for survival for at least 5 years.

Extra diagnostic assessments (imaging and laboratory tests) should be done for all subjects presenting signs and/or symptoms of relapse at the discretion of the investigator and as per clinical practice. Patients in both groups should be instructed to contact their study center if they experience any symptoms suspicious of recurrence.

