## 20 APPENDICES

1. Schedule of assessments
2. Data and Safety Monitoring Board (DSMB) charter

**APPENDIX 1:** Schedule of assessments – These are study specific assessments, and all routine follow up assessments according to national guidelines must also be performed.

| Assessments:                                                                                                                                    | Baseline
(within 28
days of
study
treatment
start)                     | 3
months
+/- 28
days (g)
Only
biomarker
patients | 6
months
+/- 28
days
(g) | 12
months
+/- 28
days
(g) | 18
months
+/- 28
days
(g) | 24
months
+/- 28
days
(g) | 30
months
+/- 28
days
(g) | 36
months
+/- 28
days
(g) | 48
months
+/- 28
days
(g) | 60
months
+/- 28
days
(g) |
|-------------------------------------------------------------------------------------------------------------------------------------------------|---------------------------------------------------------------------------------------|-----------------------------------------------------------------------------|--------------------------------------|---------------------------------------|---------------------------------------|---------------------------------------|---------------------------------------|---------------------------------------|---------------------------------------|---------------------------------------|
|                                                                                                                                                 | Adjuvant treatment is started within 12 weeks after last melanoma related surgery (d) |                                                                             |                                      |                                       |                                       |                                       |                                       |                                       |                                       |                                       |

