d) Final surgery is defined as excision and/or sentinel node biopsy, lymph-node dissection or metastasectomy. ~~For neoadjuvant treated patients, randomization is performed within 6 weeks.~~

e) Brain must be included in the baseline scan and at 24 months. To be performed according to clinical routines and this is the mandatory minimum schedule.

- f) To be performed within 28 days for adjuvant and 8 weeks for neoadjuvant patients respectively prior to study treatment start~~randomization~~.
- g) Time points from study treatment start, +/- 8 weeks allowed for neoadjuvant treated patients.
- h) Treatment related serious adverse events during treatment and up to 6 months after treatment will be reported.
- i) And at relapse.
- j) Highly sensitive urine or serum/plasma pregnancy test for WOCBP.
- k) Only applicable for standard arm.

**APPENDIX 2:****Data and Safety Monitoring Board (DSMB) Charter**DSMB organization:

|                                                             |                                                                                   |
|-------------------------------------------------------------|-----------------------------------------------------------------------------------|
| Principal Investigator                                      | [name]
Uppsala University Hospital
[contact] |
| Site-specific Principal Investigator                        |                                                                                   |
| Sponsor Representative                                      | [name]                                                                   |
| Project Managers                                            | [name]                                                                   |
| Biostatistician                                             | [name]                                                                   |
| Independent Members (subjected to change during the trial): |                                                                                   |
| [name], [name], [name] |                                                                                   |

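### Some inclusion criteria depend on the date treatment starts, which falls after randomisation, so a patient eligible when randomised can fail eligibility later with the arm known

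*Protocol*

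**What the plan says.** **Order of events.** Section 8.1 has randomisation done locally in the data capture system "before start of adjuvant treatment and stratified according to tumour stage". The study follow-up scheme places it at an early visit: "A baseline visit 1-11 weeks after the last melanoma-related surgery is scheduled for study information, inclusion and randomization".

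**Criteria that look past randomisation (section 7.2).**
- Criterion 10: "The patient must be randomized and start systemic study treatment within 12 weeks after final surgery (including neoadjuvant patients".
- Criterion 11: patients must be off immunosuppressive steroid doses "for a minimum of 14 days prior to start of study treatment drug administration".
- Criterion 6: "A complete physical examination within 28 days prior to start of study treatment randomization".
- Criterion 9, for patients without neoadjuvant treatment: "disease-free status documented by radiological assessment within 28 days prior to start of study treatment randomization". For neoadjuvant patients the window reads 6 weeks, with an 8 struck out.

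As they stand, criteria 6 and 9 name both treatment start and randomisation.

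**Appendix 1.** The first column is headed "Baseline (within 28 days of study treatment start" and contains consent and the check of inclusion and exclusion criteria. Footnote f says of imaging: "To be performed within 28 days for adjuvant and 8 weeks for neoadjuvant patients respectively prior to study treatment start", with randomisation struck out after it. The follow-up scheme shows the same replacement and the same 8 weeks.

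**Analysis (section 11).** The primary efficacy analyses use per-protocol patients, with intention-to-treat as the sensitivity analysis. DMFS and RFS are both timed from start of treatment.

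**The concern.** Eligibility should be settled before allocation. Here, parts of it are settled by a date that lies after allocation and that the site can influence. If the start slips, the site must choose between accepting an expired examination or scan, repeating it, or declaring the patient ineligible. It makes that choice knowing the arm.

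Three features of this trial make that more than a formality. A patient who has failed an inclusion criterion is an obvious candidate for exclusion from a per-protocol primary set. A relapse found on a repeat scan before the first dose precedes time zero, and a patient who never starts has no time zero. There is also a conceivable arm-related motive: section 6 records the patient organisation's expectation that some patients may fear an inferior treatment, and section 15.2 gives patients who withdraw the control-group treatment.

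**Working it through.** The protocol states no interval from randomisation to first dose, so there is no planned figure to reproduce. The check is date arithmetic on the stated windows.

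**Inputs**
- Latest treatment start: week 12 after final surgery (section 7.2, criterion 10).
- Randomisation visit: weeks 1 to 11 after surgery (study follow-up scheme).
- Baseline visit to treatment start: 28 days (Appendix 1, column heading).
- Imaging validity without neoadjuvant treatment: 28 days (criterion 9; Appendix 1, footnote f).
- Imaging validity after neoadjuvant treatment: 6 weeks in criterion 9, 8 weeks in the follow-up scheme and footnote f.

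**Longest gap between randomisation and first dose**
- From section 7.2 and the follow-up scheme alone: 12 - 1 = 11 weeks.
- If the Appendix 1 heading applies to the visit at which patients are randomised: 28 / 7 = 4 weeks.
- The two readings differ by 11 - 4 = 7 weeks.

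The shorter reading has good support. The baseline column contains the eligibility check, and the follow-up scheme puts inclusion and randomisation at the baseline visit. Also, if criterion 9 counts from treatment start, a patient without neoadjuvant treatment whose only scan precedes randomisation cannot have a gap above 28 days without a repeat scan after allocation.

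**Does the 28-day reading remove the problem?** No. That limit also counts back from treatment start, so it too can be breached after allocation. Two cases:
- Scan 20 days before randomisation, first dose 10 days after it: 20 + 10 = 30 days, which exceeds 28. The patient met the imaging window when randomised and fails criterion 9 at first dose, if treatment start is the anchor.
- Randomised in week 11, first dose after week 12: a slip of little more than one week fails criterion 10, whichever anchor applies to criteria 6 and 9.

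**Scale.** The protocol gives no slippage rate. Assuming that 2% to 5% of randomised patients miss a window, 0.02 x 1880 = 38 and 0.05 x 1880 = 94 patients would be affected, both arms together. For comparison, the 4-point margin in section 11.1 corresponds to 0.04 x 940 = about 38 events in one arm at 2 years. The first range counts patients and the second events, so the comparison shows order of magnitude only and is not an estimate of bias.

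**The case against.** Four points can fairly be made for the protocol.

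**The 11-week gap is not the only reading.** A reader of section 7.2 and the follow-up scheme might infer that 11 weeks is simply allowed. Appendix 1 does not support that, because its baseline heading limits the interval to 28 days if it covers the randomisation visit. This stands: 11 weeks is one of two readings, not the established gap.

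**Criteria 6 and 9 are not cleanly anchored to treatment start.** Their wording names both events and may be a tracked-change remnant. The strike-outs in the follow-up scheme and footnote f suggest that treatment start is meant, but the criteria do not settle it. This also stands. It does not touch criteria 10 and 11, which refer to treatment start or first dose without ambiguity.

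**Nothing says that a late starter becomes ineligible or leaves the analysis.** Section 14.4 has deviations summarised and reported, and membership of the per-protocol set may be defined in the statistical analysis plan. A reader might infer that these patients count as never having been eligible; the protocol does not say so. But it does not say the opposite either. Placing the 12-week start among the inclusion criteria invites that treatment, and an analysis plan cannot make criterion 10 decidable at randomisation.

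**No differential mechanism is shown.** Both arms receive the same drugs on the same schemes until month 6 (month 4 after surgery for neoadjuvant patients), and section 8.2 has drug and dosing interval chosen before randomisation. Most reasons for a late first dose would be unrelated to arm. A reader might infer biased selection from the fear of inferior treatment noted in section 6; that is plausible but undemonstrated.

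**Conclusion.** The point holds in limited form. Criteria 10 and 11 certainly, and criteria 6 and 9 apparently, depend on a date after randomisation, so eligibility can change once the arm is known. The exposed interval is up to 28 days or up to 11 weeks, depending on which part of the protocol governs; it would be zero if eligibility were fixed at randomisation.

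The effect on the result depends on the per-protocol primary set and the treatment-start time origin. Neither the number of patients affected nor any imbalance between arms can be derived from the protocol. That the arm is known is inferred from the absence of any described blinding; the protocol does not call the trial open-label. This is a worthwhile, inexpensive improvement, not a demonstrated bias.

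**What to change.** 1. Word every inclusion criterion so that it can be answered on the day of randomisation.
2. Move the requirement to start treatment within 12 weeks of surgery from the inclusion criteria to the conduct requirements.
3. State that a late start, or an examination or scan that expires after randomisation, is a protocol deviation that neither makes the patient ineligible nor by itself removes the patient from the primary analysis.
4. Reconcile section 7.2, the study follow-up scheme, and the Appendix 1 column heading and footnote f on three matters: the anchor date, the neoadjuvant imaging window (6 versus 8 weeks), and the permitted interval from randomisation to first dose. The sponsor should set the values.

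The cost is amendment wording and one date check in the eCRF. On the downside, some sites will have to take consent first and randomise closer to the first dose, and the primary set will keep a few patients who start late.
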